#### *Work package 2 (WP2)*

The fourth milestone (M4) will be targeted for before the end of the clinical study and consists of the setup of appropriate template database structures for import of the data that will be needed for the health economy analysis. This will allow an efficient economic evaluation study shortly after completion of the clinical study and is planned within the 4 year time frame and of the study (Milestone M5 and deliverable D2).

In the unlikely event of premature interruption of the study, the health economic analysis will be performed after the safety interim analysis on which the decision to stop was based. Previous experience in detailed analyses of healthcare resource utilization in large randomized clinical studies, as well as close collaboration with the Finance & Accounting department and the pharmacies of all participating hospitals will guarantee successful and timely accomplishment of this deliverable.

#### *Work package 3*

The mechanistic studies will be coordinated by and performed in the Leuven Laboratory of Intensive Care Medicine and in the Erasmus MC. Part of the mechanistic analyses will be systematically performed throughout the study. More specifically, leukocyte function tests require the fresh isolation of leukocytes and hence will be performed in parallel with work package 1. Thus, these analyses will be completed at the end of the clinical study (milestone M6 and deliverable D3). The samples needed for the other mechanistic studies will be taken throughout the clinical study and as deliverable 4 (D4) will be available together with M3 and D1. The other mechanistic studies involving the investigation of autophagy, genetics and cytokines in relation to the inflammatory response, as well as of the neuroendocrine axes will be planned and started in the last phase after completion of the clinical study.

In (the unlikely) case the study would be terminated prematurely, the mechanistic studies will be even more important, as the clinical community will ask for due explanations for harm caused during the study. Therefore, in any case they will be started shortly after all clinical data have been collected.

[figure not shown]

## **15. STUDY POPULATION**

### **15.1 Population Base**

The patient group of critically ill children (0 – 18 yrs), represents a significant proportion of the ICU population. In 2010, the 10-bed Leuven PICU admitted 527 critically ill children, the majority requiring artificial ventilation. 61% of the cases were admissions after cardiac surgery. Individual critically ill children had a median ICU stay of 3 days (inter-quartile range of 2-6 days) (mean 5.5 days). In the 35-bed PICU of the University of Rotterdam 1700 critically ill children were admitted in 2010 of which 600 (35.3%) were ventilated. Patients stayed in the PICU for a median of 2 days (mean 7.8 days). We anticipate an inclusion rate of 200-250 patients per centre per year.

### **15.2 Inclusion criteria**

All critically ill children admitted to the participating PICUs are evaluated for nutritional risk and eligibility for inclusion in this study. All critically ill children, with nutritional risk score (STRONGkids® see appendix) 2 or more, who are not able to take oral nutrition and are expected to stay in PICU for more than 24h are eligible for inclusion.

### **15.3 Exclusion criteria**

Exclusion criteria are a “do not resuscitate” code at the time of PICU admission, expected death within 12 hours, re-admission to the PICU after previously being participating in the PEPaNIC trial (except when < 48 hours after the initial discharge and still in the intervention window of the first 7 days), transfer from another PICU after a stay of more than seven days, ketoacidotic or hyperosmolar coma on admission or inborn metabolic diseases requiring specific diet, premature newborns (<37 weeks gestational age), patients on Total Parenteral Nutrition for >7 days prior to inclusion, short bowel syndrome or other conditions which required home-PN.

### **15.4 Sample size calculation**

The sample size (N=1440, 720 per arm) is calculated in order to detect, with at least 80% power (one-tailed; the two-tailed power is 70%) and 95% certainty, a reduction in PICU infections from 20% to 15% and, with at least 90% power (two-tailed) and 95% certainty, a reduction in mean duration of stay in PICU of 1 day. With this sample size, and for safety reasons, also any substantial impact on mortality (increase or decrease with an absolute +/- 2%, although unexpected taken the adult data), can be excluded with a power of around 62-75% depending on the true mortality in the total population. We plan to calculate the true power of the study for detection of any eventual smaller differences in these outcomes.

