## 20. STATISTICAL ANALYSIS

### 20.1 Descriptive statistics

The current statistical analysis plan comprises the primary and secondary clinical endpoints of this RCT (work package 1). These include the acute clinical effects of the intervention during ICU stay and hospitalization, including survival up to 90 days after randomization.

The sample size (N=1440, 720 per arm) is calculated in order to detect, with at least 80% power (one- tailed; the two-tailed power is 70%) and 95% certainty, a reduction in PICU infections from 20% to 15% and, with at least 90% power (2-tailed) and 95% certainty, a reduction in mean duration of stay in PICU of 1 day. With this sample size, and for safety reasons, also any substantial impact on mortality (increase or decrease with an absolute  $\pm 2\%$ , although unexpected taken the adult data), can be excluded with a power of around 62-75% depending on the true mortality in the total population. We plan to calculate the true power of the study for detection of any eventual smaller differences in these outcomes.

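### The stated 90% power for a 1-day shorter PICU stay cannot be reproduced: it needs an SD of at most 5.85 days, which the protocol's own skewed figures make unlikely, and it is not the power of the planned Cox test

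*Supplement*

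**What the plan says.** Final protocol, section 15.4: "The sample size (N=1440, 720 per arm) is calculated in order to detect" two effects. The first is on infections, "with at least 80% power (one-tailed; the two-tailed power is 70%) and 95% certainty, a reduction in PICU infections from 20% to 15"%. The second is on stay, "with at least 90% power (two-tailed) and 95% certainty, a reduction in mean duration of stay in PICU of 1 day". Section 20.1 repeats the target of "a reduction in mean duration of stay in PICU of 1 day". Neither section gives an SD, a distribution, a test, a hazard ratio or a number of events for stay.

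The only length-of-stay data are in section 15.1. For Leuven: "Individual critically ill children had a median ICU stay of 3 days (inter-quartile range of 2-6 days) (mean 5.5 days"). For Rotterdam: "Patients stayed in the PICU for a median of 2 days (mean 7.8 days"). Both describe 2010 PICU admissions. Nothing is given for Edmonton.

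Sections 14 (Primary Objective), 18.1.1 and 20.2 define the co-primary endpoint as time to discharge alive, taken as time to being ready for discharge. It is analysed by Cox regression, with non-survivors censored beyond the longest stay among survivors.

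On mortality, section 15.4 says that a change of 2 percentage points in either direction "can be excluded with a power of around 62-75% depending on the true mortality in the total population". No mortality rate is stated.

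**The concern.** A power figure for a difference in means cannot be interpreted without the SD. PICU stay usually has a long right tail, and here the mean is nearly twice the median in one centre and almost four times the median in the other. A tail that pulls the mean so far from the median normally brings a large SD, and power for a fixed 1-day difference falls quickly as the SD grows.

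There is a second gap. The primary analysis of stay does not compare means. It compares the rate of discharge alive, and how a 1-day shift in the mean translates into a hazard ratio depends on the shape of the distribution.

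The introduction (section 13) calls the trial sufficiently powered for length of stay, and the stated 90% is the basis for that. If the figure is too high, or belongs to another test, a null result on stay could be over-read as evidence of no effect. The mortality statement carries the same risk: it speaks of excluding an effect, while the planned chi-square and Cox analyses can only detect one.

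**Working it through.** **Inputs.** 720 per arm, two-tailed 5%, difference of 1 day (15.4); means and medians (15.1). The equal centre mix, the distribution shapes, the proportion discharged alive and the mortality rates are assumptions.

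**1. Check on the formula.** Infections, 20% vs 15%, unpooled SE = √(0.20×0.80/720 + 0.15×0.85/720) = 0.01995. One-tailed power = Φ(0.05/0.01995 − 1.645) = 80.4%; two-tailed = Φ(0.05/0.01995 − 1.960) = 70.6%. The plan's 80% and 70% reproduce.

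**2. SD needed for the stay claim.** Power = Φ(1/(SD·√(2/720)) − 1.960). Setting this to 90%:
SD = √360 / (1.960 + 1.2816) = 18.97/3.2415 = **5.85 days**.

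**3. SDs matched to section 15.1.**
- Exponential: SD = mean, so 5.5 and 7.8. This matches the means only.
- Gamma: the shape that gives the stated mean/median ratio is 0.632 (Leuven) and 0.310 (Rotterdam). SD = mean/√shape = 6.9 and 14.0.
- Weibull: shape k solves Γ(1+1/k)/(ln 2)^(1/k) = mean/median, so k = 0.785 and 0.513. SD = 7.1 and 16.8.
- Log-normal: SD = mean·√((mean/median)² − 1) = 8.5 and 29.4.

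For an equal mix, the within-centre SD is √((SD₁² + SD₂²)/2); for example √((5.5² + 7.8²)/2) = 6.75.

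| Distribution | Leuven SD (power) | Rotterdam SD (power) | Mix SD (power) | Per arm for 90%, mix |
|---|---|---|---|---|
| Exponential | 5.5 (93%) | 7.8 (68%) | 6.75 (80%) | 958 |
| Gamma | 6.9 (78%) | 14.0 (27%) | 11.1 (40%) | about 2,570 |
| Weibull | 7.1 (76%) | 16.8 (20%) | 12.9 (31%) | about 3,500 |
| Log-normal | 8.5 (61%) | 29.4 (9%) | 21.6 (14%) | about 9,840 |

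**4. How small the SD could be.** An SD cannot be below |mean − median|, which is 5.8 days in Rotterdam. At exactly 5.8, power is 90.5%, but this floor requires half the children to stay exactly 2 days and the other half exactly 13.6. For Leuven, the quartiles and mean allow 3.5 days at the least. The pooled minimum is √((3.5² + 5.8²)/2) = 4.8, with 98% power. A log-normal fitted to Leuven's IQR gives SD 4.1 with the stated median (implying mean 4.2, not 5.5) or 5.3 with the stated mean; power is over 99% or 94%.

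**5. The planned test.** For a Cox model with 1:1 allocation, the hazard ratio detectable with 90% power is exp(2×3.2415/√events). With 1,370 discharges alive (about 95% of 1,440, assumed) this is exp(6.483/37.01) = **1.19**. If stays were exponential, a 1-day shorter mean would be:
- at mean 5.5: HR 5.5/4.5 = 1.22, power 95–97% for 0–10% deaths;
- at mean 7.8: HR 7.8/6.8 = 1.15, power 70–74%.

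In a log-rank simulation with log-normal stays, proportional shortening and 5% deaths, power was about 62% (Leuven figures) and 17% (Rotterdam figures). The same 1-day target thus gives anything from 17% to 97%, depending on an unstated assumption.

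**6. Mortality, 720 per arm, difference of 2 points.** At 3% vs 5%, SE = √(0.03×0.97/720 + 0.05×0.95/720) = 0.01031, giving 62% one-tailed and 49% two-tailed. But 1.1% vs 3.1% gives 76% two-tailed, and 1.9% vs 3.9% gives 62% two-tailed. The range 62–75% can therefore arise either way.

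**The case against.** A reader might infer that 90% power is impossible on the protocol's own figures. The documents do not support that. Mean, median and IQR do not fix an SD; the smallest admissible values satisfy the 5.85-day limit, and Leuven's IQR taken alone fits an SD below it. The log-normal matched to Leuven's mean and median has quartiles of 1.4 and 6.3 rather than the stated 2 and 6, so no single curve should be leaned on. This stands, and it is why the conclusion is unlikely rather than impossible. It does not rescue the figure: the minimum distributions are implausible, and the IQR fit says nothing about Rotterdam, where even SD = mean gives 68%.

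The population also differs. Section 15.1 describes all 2010 admissions at two of three centres, whereas eligible children are a subset (section 15.2: nutritional risk, no oral intake, expected stay over 24 hours). Their spread could be smaller or larger. This too stands; it is a reason for the plan to name the SD it used.

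The mismatch with the Cox test does not in itself show low power, since some assumptions give over 95%. It shows only that the power of the primary analysis of stay is unstated.

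On mortality, it is tempting to say that 62–75% is one-tailed power, as 3% vs 5% suggests. Other low rates give the same range two-tailed, and no rate is stated, so this is not shown. The introduction speaks of detecting a doubling or halving of mortality, so the language of exclusion in 15.4 may be loose wording.

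Finally, section 15.4 promises a later calculation of the power for smaller differences. That supplies no SD for the present claim. Nor does the SAP, which covers a later secondary analysis.

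**Conclusion.** The point holds in this form: the 90% power for a 1-day shorter mean stay cannot be reproduced, requires an SD of at most 5.85 days, and is unlikely given the skewed stays that the protocol itself reports. For an equal mix of the two centres, plausible shapes give about 80% at best and 40% to 14% when both mean and median are matched. These values rest on the 2010 admissions standing in for enrolled children, on an equal mix, and on the distributions chosen.

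Separately, and without any such assumption, the figure is not the power of the planned Cox analysis, for which neither a hazard ratio nor an event count is given.

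The infection power reproduces and is not in question. The mortality range cannot be checked because its rates and sidedness are missing. The point does not show that the trial is too small for its Cox analysis of stay.

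**What to change.** In sections 15.4 and 20.1:

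- **Stay.** Replace the 90% figure with the detectable effect for the planned test. For example: with 1,440 children and about 1,370 discharged alive (95% assumed), the trial has 90% two-tailed power for a discharge hazard ratio of about 1.19.
- **1-day difference.** Keep it only with its SD, the source of that SD, and power over a plausible range, such as 80% at SD 6.75, 61% at 8.5 and about 40% at 11.
- **Mortality.** State the assumed rates and the sidedness behind 62–75% (for example, 3% vs 5% gives 62% one-tailed and 49% two-tailed). Speak of detecting rather than excluding a 2-point change, and report the risk difference with its 95% confidence interval.

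The hazard ratio of 1.19 is solved from the sample size, so the investigators should say whether an effect of that size matters clinically. The cost is protocol wording and probably a less favourable stated power. Sample size, endpoints and analyses do not change.

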In our study we aim to evaluate whether the current practice of Early PN in critically ill children really provides clinical benefits over a strategy of withholding PN during the first 7 days in the paediatric ICU. The evaluation will be done in a multicentre randomized controlled trial performed in three large expert tertiary referral paediatric ICUs. The study will be statistically sufficiently powered to detect differences in clinically relevant outcome variables (the rate of new infections and the length of stay in the ICU). The trial will also be able to detect a doubling or halving of the mortality rate with a respectable statistical power (details on statistical power are given in the description further on). The results of this randomized controlled trial will provide, for the first time, high quality evidence for practice guidelines for nutrition in critically ill children. It will answer the question whether Early PN is beneficial, harmful or neutral in comparison with the new therapy

of withholding PN during the first week of critical illness. In weighing this evidence for current nutritional practice, this study will take into account 1) the short-term as well as the long-term health effects of the feeding protocols, 2) costs, and cost-effectiveness and 3) some insights into the underlying mechanisms of the observed clinical differences.

Also, one of the goals of the PEPaNIC study is to look into the tolerance for enteral nutrition (EN). In critically ill children EN is preferred because it is more physiological, presents fewer complications, leads to a better outcome and is less expensive than PN. However, EN often fails in this patient group due to impaired gastrointestinal (GI) motility, digestion and absorption following ischemia, inflammation or starvation leading to intolerance to EN. To improve future EN tolerance in critically ill children we have to gain insight in parameters of influence in this complex process.

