### **STUDY DESIGN**

This study is a large, three-centre, non-blinded, randomized, controlled study. The study intervention will last for a maximum of 7 days per patient, and the entire study (final patient completed study) is anticipated to last 4 years, excluding the long-term follow-up, the health-economic analysis and the completion of the mechanistic studies. (See figure)

Consecutive patients are randomly assigned to one of the two treatment study groups using a digital system with central, computerised randomisation. Randomisation – in a one to one allocation ratio - is performed per centre and using permuted blocks of 10 per diagnostic stratum. The block size remains unknown to bed-side physicians and nurses, responsible for patient recruitment and therapy assignment.

The “early PN” strategy will be the nutritional management currently applied in the participating centres, acting as “control”.

The “late PN” strategy comprises initiation of this strategy only after day 7 in PICU.

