### ***General rules of the statistical analysis***

All analyses will be done on intention to treat basis. The analyses will be performed on the whole set of patients and by subgroups of patients based on the primary diagnostic categories used as prognostic factors for stratification and on septic/non-septic groups of patients.

A consort diagram will be reported. The data file will be finalised 90 days after inclusion of the last patient. To assess compliance with the study protocol, the amounts of PN and EN actually given in the two study groups during the intervention window of 7 days will be reported as absolute numbers and percentages of target calories. Discrete variables will be summarised by frequencies and percentages and analysed by (exact) Chi- square test or logistic regression analysis. Continuous variables will be summarised by use of either mean or standard deviations (SD) or median and interquartile range as appropriate and compared using Student's t-test or Mann-Whitney-U test, as appropriate. Time to event analysis will be performed by Cox proportional hazard analysis. All outcomes will be analysed in an uncorrected manner as well as (jointly) corrected for risk factors (type and severity of illness, age, on admission nutritional status and risk scores). *A priori* defined subgroup analyses will be performed for patients admitted to ICU after cardiac surgery as compared with all other patients; for patients with and without sepsis upon admission; for patients with contra-indications for EN on admission or not. For all endpoints, differences will be considered statistically significant whenever the p-value is lower than 0.05 without correction for multiple testing.

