### Safety endpoints

Safety endpoints comprise vital status, hypoglycaemia, serious adverse events and complications related to the mode of nutrition. Survival up to 90 days after randomization in both treatment groups will be compared by Kaplan Meier survival plots. The impact of "late PN" versus "early PN" will be analyzed, with and without correction for risk factors, by Cox

proportional hazard analysis. In addition, we will record vital status at ICU and hospital discharge, and will analyze differences with Chi-square testing. As the randomized study intervention only takes place during a time window up to the 8th day in ICU, we also plan to analyze early lethality within this time window in the intention to treat population as part of the safety analysis.

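### The protocol says a 2-point mortality change can be excluded with 62-75% power, but that figure is power to detect, and no planned analysis compares a confidence bound with 2 points

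*Supplement*

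**What the plan says.** Section 15.4 of the final protocol fixes 720 patients per arm and then turns to mortality as a safety matter. Its target is "any substantial impact on mortality (increase or decrease with an absolute +/- 2%, although unexpected taken the adult data". The claim made there for an effect of this size is that it "can be excluded with a power of around 62-75% depending on the true mortality in the total population". Section 20.1 repeats the claim ("can be excluded with a power of around 62-75"). Neither section gives the assumed mortality, the sidedness of the mortality calculation or a formula.

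Section 13 describes the mortality power differently: "The trial will also be able to detect a doubling or halving of the mortality rate with a respectable statistical power".

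The analysis is set out under 20.1. Survival to 90 days is compared by Kaplan-Meier plots and Cox regression. For vital status at ICU and hospital discharge the investigators "will analyze differences with Chi-square testing". The only decision rule is that "differences will be considered statistically significant whenever the p-value is lower than 0.05 without correction for multiple testing". No section sets a margin for mortality or a rule based on a confidence interval.

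The SAP covers a secondary analysis of undernourished children and weight change. It lists 7-day and 90-day mortality as safety outcomes, again with difference tests at 0.05, and does not supply the missing rule.

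**The concern.** To exclude an effect of a given size is a statement about a confidence bound: the interval for the difference must lie inside that size. A test of no difference cannot provide this. When it is non-significant, the data may still be compatible with an excess of more than 2 points. The protocol therefore promises a conclusion that none of its planned analyses can reach.

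Vital status is the first-named safety endpoint in a trial that withholds standard parenteral nutrition from critically ill children for a week. What may be said about mortality at the end matters, and it should follow from an analysis that was planned.

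**Working it through.** **Inputs.** n = 720 per arm, 1:1 allocation, a difference of 2 points in either direction, stated power 62-75% (15.4); significance at 0.05 (20.1). Baseline mortality and the sidedness of the mortality power are not given. Both are treated as assumptions below.

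**Step 1: check the formula on a figure that can be reproduced.** With p̄ the mean of the two rates,

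power = Φ{ [|p1 − p2| − z·√(2p̄(1−p̄)/n)] / √[(p1(1−p1) + p2(1−p2))/n] }.

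For infections, 20% vs 15%:
- Two-sided: (0.05 − 1.96 × 0.02003)/0.01998 = 0.54, power 70%.
- One-sided: (0.05 − 1.645 × 0.02003)/0.01998 = 0.85, power 80%.

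Both agree with 15.4.

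**Step 2: what 62-75% corresponds to.** The same formula, solved for pairs of rates 2 points apart:

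| Reading | 75% power | 62% power |
|---|---|---|
| Two-sided 5% | 1.12% vs 3.12% (mean 2.12%) | 1.89% vs 3.89% (mean 2.89%) |
| One-sided 5% | 1.8% vs 3.8% (mean 2.8%) | 2.9% vs 4.9% (mean 3.9%) |

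For example, 1.12% vs 3.12% two-sided gives (0.02 − 1.96 × 0.00759)/0.00757 = 0.68, power 75%. The stated range is what a power-to-detect calculation returns at plausible rates. The same figures mean that a true 2-point difference is missed 25-38% of the time.

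**Step 3: chance of exclusion if the arms are truly equal.** With common mortality p and SE = √(2p(1−p)/720):
- one direction: Φ(0.02/SE − 1.96)
- both directions: 2Φ(0.02/SE − 1.96) − 1

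At p = 2.12%, SE = 0.00759 and 0.02/SE = 2.63, so one direction is 75% and both are 50%. At p = 2.89%, SE = 0.00883 and 0.02/SE = 2.26, so one direction is 62% and both are 24%.

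Full binomial enumeration with 95% intervals gives:

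| Common mortality | One direction, Newcombe | One direction, Wald | Both, Newcombe | Both, Wald |
|---|---|---|---|---|
| 2.12% | 71% | 75% | 42% | 50% |
| 2.89% | 59% | 62% | 18% | 25% |

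On the one-sided reading, with a 90% interval at mean mortality 2.8-3.9%, the formula again gives 62-75% for one direction and 24-50% for both.

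**Step 4: how often the p-value and the bound disagree.** With equal arms at these two rates, about 95% of trials are non-significant. In 26-39% of trials (Newcombe) or 22-35% (Wald), the test is non-significant while the 95% CI still reaches +2 points.

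**Step 5: doubling or halving (section 13).** By the Step 1 formula, two-sided:
- Power for a halving runs from 21% at a baseline of 1.1% to 59% at 3.9%.
- Power for a doubling runs from 37% to 88% over the same baselines.

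One-sided power for a halving is about 70% at 3.8% and 80% at 4.9%.

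**The case against.** The strongest reply is that this is one badly chosen verb. Section 13 speaks of detecting, and the sentence after the claim in 15.4 also speaks of detection, so power to detect was evidently meant. The protocol states openly that this power is only 62-75%, which discloses the miss rate. The safety question is excess mortality under late PN, which is one direction. If *increase or decrease* means each direction separately, 62-75% is about right as the chance of excluding either one when the arms are equal. Mortality is a safety endpoint rather than a primary or non-inferiority endpoint, and a DSMB reviews unblinded ICU and hospital mortality after patient 720.

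Much of this stands. It limits the point in four ways:

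- A reader might infer that the investigators will treat p>0.05 as proof of mortality safety. No section says so; 20.1 only defines when a difference is significant.
- A reader might infer that 62-75% is miscalculated. It is not: it is coherent as power to detect, and nearly right for one-direction exclusion. The shortfall concerns excluding both directions together.
- A reader might merge the two interval methods into a single range of 18-50%. They are separate methods, applied at a mortality the protocol does not state.
- A reader might infer that power for a halving is below 60% at every compatible baseline. That holds two-sided but fails one-sided at 3.8-4.9%, and 15.4 leaves the mortality sidedness open.

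What the reply does not meet is that 15.4 and 20.1 both use the language of exclusion. Even one-direction exclusion needs a bound compared with 2 points, and none is planned.

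**Conclusion.** The claim in 15.4 and 20.1 is wrong as written. The figure of 62-75% is power to detect a 2-point mortality difference, and the planned difference tests cannot exclude one. Under equal arms and the two-sided reading, a 95% CI would exclude one chosen direction in 59-71% (Newcombe) or 62-75% (Wald) of trials, and both directions in only 18-42% or 25-50%.

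These sizes rest on mean mortality of about 2.1-2.9%, back-solved from the stated power because the protocol gives no baseline. The lack of any interval-based rule does not depend on that assumption. The wording in section 13 cannot be judged until baseline and sidedness are stated. The primary efficacy inference is unaffected.

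**What to change.** 1. In 15.4 and 20.1, replace the exclusion claim with 62-75% power to detect a 2-point difference, and state the assumed mortality and the sidedness.
2. Under the safety endpoints in 20.1, add the absolute difference in ICU, hospital and 90-day mortality, each with a two-sided 95% CI by a named method. Section 22.1 plans to record 90-day vital status for all patients, so a difference in proportions is available beside the Cox model.
3. State that a 2-point increase is excluded only if the interval lies below +2 points, and a 2-point decrease only if it lies above −2 points. Otherwise the mortality effect is reported as inconclusive.
4. In section 13, keep the statement on doubling or halving only if the stated baseline and sidedness support it.

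The cost is wording in three sections and one confidence interval per mortality endpoint. No new data or patients are needed. The safety claim becomes less favourable, but the planned analysis can then support it.
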